## Abstract

**Background:**

The increasing rate of dementia and high health and social care costs call for effective measures to improve public health and enhance the wellbeing of people living with dementia and their relational networks. Most postdiagnostic services focus on the condition and the person with dementia with limited attention to the caring spouse or partner. The key focus of the study is to develop a guide for couples where one partner has a diagnosis of dementia. This couple management guide is delivered in the form of an app, DemPower.

**Objective:**

This study aims to investigate the feasibility and acceptability of DemPower and to assess the criteria for a full-integrated clinical and economic randomized control trial. DemPower couple management app will be introduced to couples wherein one partner has dementia.

**Methods:**

The study will recruit 25 couples in the United Kingdom and 25 couples in Sweden. Couples will be given 3 months to engage with the app, and the amount of time taken to complete the guide (can be <3 or >3 months) will be reviewed. A set of outcome measures will be obtained at baseline and postintervention stages.

**Results:**

The proposed study is at the recruitment phase. The DemPower app is being introduced to couples from consultation groups at a pretrial phase for identifying any bugs and exploring if any navigation challenges exist. The feasibility testing will begin in April 2018.

**Conclusions:**

The study will determine how much support couples need to engage with DemPower and whether or not they make use of it in their everyday lives. If there is support for app use, a future study will assess whether it is superior to “usual care.”

**Trial Registration:**

International Standard Randomized Controlled Trial Number (ISRCTN): 10122979; http://www.isrctn.com/ISRCTN10122979 (Archived by WebCite at http://www.webcitation.org/70rB1iWYI)

**Registered Report Identifier:**

RR1-10.2196/9087

## Introduction

The prevalence of dementia is rising globally with increases in the average age of the world’s population and is estimated to reach 131.5 million by 2050 [1]. The evidence base for high-income countries (United States, United Kingdom, Netherlands, and Sweden) suggests a declining trend in age-specific incidence [2,3]. In the United Kingdom and Sweden, two-thirds of all people with dementia are aged over 80 years [4,5] and more than 50% live alone at home or with their care partner [6,7]. In 2013, the total health and social care cost of dementia in the United Kingdom was estimated to be £26.3 billion, of which 44% were unpaid care costs [5,8]. In Sweden, during 2012, the estimate for health and social care costs was SEK 52 billion, of which informal care was 16.7% [2]. The financial costs to health and social care that are attributed to dementia are likely to continue to increase in future years unless effective measures are undertaken to improve public health [4,9]. Accordingly, a well-defined approach needs to be adopted to manage the implications of dementia on societal systems and organizations, including the wellbeing of people living with dementia and their relational networks [1].

The national and international push for early diagnosis and intervention in dementia has incentivized programs and strategies to improve diagnostic rates and quality of life for people living with dementia and their families. In the United Kingdom, some of these strategies involve public awareness campaigns, training health and social care professionals, memory assessment and support services, internet-based forums for caregivers, and creating dementia-friendly infrastructures, spaces and technology [10-15]. However, despite these improvements, some studies indicate that people with a recent diagnosis of dementia are largely left on their own to manage their condition [16,17] and are only (re)visited by statutory services once a crisis at home occurs [7]. This is an interesting paradox as the demographic data suggest that most people with dementia want to live in their own home and neighborhood for as long as possible. It is, therefore, imperative that relevant supports are made available early on during the diagnostic process, and that people living with dementia and their relational networks are made aware of available resources and services. This could prevent the occurrence of crisis situations and reduce health and social care costs.

In the United Kingdom, alongside mainstream health and social care services, some charities such as the Mental Health Foundation, Age UK and the Alzheimer’s society have long provided localized support services and opportunities for people with dementia and their families to access community engagement programs. While welcome, there remains a dearth of dyadic, couple-centered approaches [18,19], with most interventions for couples where one partner has a dementia overwhelmingly emphasizing the condition (the dementia), rather than on the needs of partners as a couple [20-24]. In Sweden, most people with dementia live in their homes, in which they require care and support. This has been identified as one of the main challenges facing primary care in Sweden [25]. To address this gap in interventions for couples, an easy to use couple management guide was developed as part of the “Living Life and Doing Things Together” project. This project is one of eight work programs within the Economic and Social Research Council (ESRC)/National Institute for Health Research (NIHR) Neighbourhoods and Dementia mixed methods study [26]. All the eight work programs are underpinned by a neighborhoods’ model [27], positioning people living with dementia and their social and relational networks at the center of the overall study aims and objectives. Informed by this approach, the current work program (6) is centered on the lives of couples who live together at home, where one partner has a diagnosis of dementia. The couple management guide developed in this study is delivered in the form of an app, DemPower*.* In this study, the intervention was tested for feasibility.

The use of mobile apps in health care, especially among people with dementia and their families, has gained prominence due to the ability of these apps to promote quality of life for the person with dementia and their families [28,29]. Some of the apps on the market include global positioning system trackers to enable people with dementia and their families to feel safe in their neighborhoods [30,31], schedule activities of daily living, communicate, and manage appointments and emergency help [32]. The wider research evidence suggests self-management resources in the form of apps, complemented with appropriate training and support, are beneficial for patients in the early to moderate stages of dementia and enhance quality of life [28,33]. This paper reports the protocol to evaluate the acceptability and feasibility of the DemPower intervention.

The overall aim of the study is to investigate the feasibility and acceptability of the app-based couple management guide DemPower among couples living together at home, where one partner has dementia. The key objectives are (1) to explore if the DemPower couple management guide is useful and acceptable to couples, (2) to assess the recruitment capability and how effective and appropriate are the outcome measures and data collection procedures, and (3) to analyze the potential for conducting an economic evaluation in the full trial.

## Methods

### Study Design

The study uses a prospective, nonrandomized feasibility design to investigate the level of uptake of DemPower among couples where one partner has a diagnosis of dementia. The methodology facilitates an assessment of study processes to explore the criteria for a full trial.

### Study Population

The study will involve couples with one partner having a diagnosis of dementia and who live together at home. We will seek to recruit a wide and diverse couple population. This extends to any type of dementia, sexual orientation, age, profession, social, cultural, and religious contexts. Participants will be enrolled regardless of comorbidities experienced by a partner with dementia and the health status of a supporting partner. We will also include participants enrolled in other research studies. The wide diversity of participants is envisaged to study a better understanding of potential participants for a future full trial. This also provides opportunities to explore population needs, compare outcomes, and inform the areas that need further development. Specific inclusion and exclusion criteria are listed in Textbox 1.

### Sample Size

As this is a feasibility study, no formal power calculation is needed. Instead, Lancaster et al [34] recommend including between 30 and 50 participants (in this study, couples) to estimate critical parameters (eg, recruitment rate; standard deviation of primary outcome) with necessary precision. This study does not aim to randomize participants, and therefore, there is no control group in this study. We will aim to recruit 50 couples across North West England and Sweden (Linköping and Norrköping). Figure 1 describes various stages of the study.

### Selection and Recruitment

#### In the United Kingdom

The recruitment of 25 couples in North West England will take place via Clinical Research Network, Joint Dementia Research network, dementia cafes, and third sector organizations. We will also advertise our study in memory clinics and through the wider project’s website and social media (Twitter) networks to identify and recruit potential participants who are interested in the study.

Staff members working at National Health Service Trusts and Clinical Research Networks will be involved in identifying people with dementia to the study, and they will use the Trust databases and the Join Dementia Register to identify potential eligible participants.

The researcher will establish contacts with staff from third sector organizations and coordinators of dementia cafes (eg, Age UK, Alzheimer’s society, Creative Mind etc). Appropriate permissions will be sought prior to addressing the group. The study poster will be displayed at these meetings, and detailed study information will be available for interested group members. The researcher will ensure that the third sector organizations’ contact source or coordinators do not communicate potential participants’ details without their prior permission.

For recruiting through advertisements, interested participants are free to contact the researcher. Contacts established in this manner will be followed up through a face-to-face meeting. At this meeting, the researcher will explain the study and hand in the detailed study information pack.

Potential participants who meet the inclusion criteria will be given information about the study and the opportunity to express an interest in taking part in the study. Potential participants will have opportunities to ask any questions they have and to discuss any aspects of the study with the researcher before they make their decision. The interested participants will be given sufficient time to make a decision and be approached again to obtain informed consent (24 hours or more after the first visit).

#### In Sweden

A total of 25 couples will be recruited from memory clinics and dementia cafes based in county Östergötland (Linköping and Norrköping) of Sweden.

The staff at the memory clinic will identify couples, contact potential participants to discuss the study, and identify couples who are interested in participating. Couples who express interest in participating will have their details passed on to the relevant researcher.

The researcher will contact study staff or coordinators within the third sector organizations (eg, dementia cafes): day care centers and family care centers within the municipalities of Linköping and Norrköping. On obtaining relevant permissions, study posters will be displayed and details of the study will be presented to the members of the group. Researchers will approach interested participants individually to assess for inclusion, discuss the study in detail, and obtain consent.

Inclusion and exclusion criteria.
**Inclusion criteria**
Couples who have a partner or spouse with a diagnosis of dementia in early to moderate stages. The stage will be identified either via clinical team during referral or through self-reportCouples who live together in their own homes (not residential care).Both partners understand and speak English (in the United Kingdom) or Swedish (in Sweden)Couples in a long-term relationship for 2 or more years
**Exclusion criteria**
Couples with one or both partners who are blind and might find it difficult to interact with DemPowerAny partner who has become completely immobile or bed-bound and may not be able to engage with suggested activitiesBoth partners having a diagnosis of dementiaCouples where one or both partners lack capacity or may have fluctuating capacity

**Figure 1 figure1:**
[figure not shown]
Study stages.

### DemPower Intervention

Living Life and Doing Things Together is a couple management guide delivered through the platform of an electronic application on a touchscreen device (Android tablet). The guide is aimed at enhancing the wellbeing as well as the relationship of couples where one partner has a diagnosis of dementia. The contents in this guide are based on couples with lived experience, available research, and practice evidence.

The objectives of the DemPower guide are (1) to help couples focus on the activities that they can do rather than what they cannot, (2) to reflect upon the strengths of their relationship, (3) help couple find ways to tackle daily activities together, and (4) to archive reflections, moments, and memories the way they would like them to be remembered.

The guide is structured under 4 primary themes and several sections within each theme, as illustrated in Figure 2. The themes and corresponding sections are introduced using storyboard techniques with a voiceover. Videos clips of couples sharing their experiences demonstrating particular situations follow storyboard illustrations. The guide makes suggestions for activities under each section. Examples of some suggested activities include games (stored on the device), links to useful information, taking pictures, writing reflections, and discussing emotions, needs and required changes to their home and their approach to daily life.

The app design facilitates various forms of user interfaces and provides users the control over font size, color, language, volume etc. The design also focuses on making the interface simple and easy to access. The interaction within the app is multimodal (voice, touch, text to speech). User-centered and participatory approaches inform the overall app design and concept.

The app and all the corresponding resources will be saved onto a portable device (tablet) prior to handing them over to the recruited couples (one tablet per couple). Researchers will provide a tutorial on how to use the device and the app. A detailed help video is inbuilt into the app. Researchers will provide a printed copy on how to use the device and the guide to all the participants. The participants may contact researchers at any time if they require technical support. The researchers will call the participants once a month to check their progress and arrange visits if required. We will recommend the participants to engage with two sections per week. They have the option to engage with a selection of sections or with the entire guide and in any order. Participants are expected to complete the guide within a period of 3 months from the date of device activation.

### Feasibility, Acceptability, and Health Outcome Measures

The goal of the study is to explore feasibility, acceptability, and usability of DemPower among couples where one partner has dementia. Using Bowen et al’s [35] suggested areas of focus for feasibility studies, Table 1 reports the approaches and measures used to assess the different aspects of the feasibility and acceptability of the DemPower intervention [35-37]. The structure in Table 1 helped to identify relevant outcomes, demonstrate how these address study objectives, and inform the choices of data collection procedures.

Two primary data sets will be generated from the study: evaluation and outcomes data. The study team designed a set of evaluation questionnaires to assess participants’ experiences with DemPower and the study processes (Multimedia Appendices 1-5). These questionnaires, DemPower, and chosen outcome measures will be tested with couples from a consultancy group for comprehension errors and bug fixing prior to the feasibility phase. The outcomes used to represent effectiveness include health-related aspects of quality of life, self-efficacy, interconnectedness, and mutuality on the part of both partners.

**Figure 2 figure2:**
[figure not shown]
Guide contents.

**Table 1 table1:** Bowen et al’s [35] feasibility criteria and study application.

Area of focus	Study application	Outcomes of interest	Data sources
Acceptability and integration	To what extent is DemPower suitable to implement in home-living couples with dementia?	Perceived acceptability and satisfaction	Evaluation Questionnaires, 3-point Likert scale
Demand	To what extent do couples consider the couple management approach and the content of DemPower as desirable support?	Perceived usability	Usage tracking data, self-reported system usability scale [38], 5-point Likert scale
		Perceived benefits of DemPower	Evaluation Questionnaires, 3-point Likert scale
Implementation and practicality	To what extent can DemPower be successfully implemented with couples living with dementia?	Willing and able to complete all the sections of the self-help guide	Dropout rates usage tracking data
		Type of, and amount of support needed by couples	Evaluation questionnaire – custom matrix
		Degree of technical errors, resources, factors influencing implementation	Researcher log
Adaption	To what extent can DemPower be used in its current state?	Degree of errors; levels of support	Researcher log; Evaluation Questionnaires, 3-point Likert scale
Efficacy	To what extent does DemPower show promise of encouraging engagement and positive effects on couples’ relationships and beliefs in managing daily life?	Impact on quality of life, relationship quality, mutuality, closeness, sense of couplehood, self-efficacy, and health status	Baseline and post intervention or end point assessments of quality of life—Quality of Life in Alzheimer´s disease [39], Care-related Quality of Life [40]; Relationship Quality and Mutuality – Mutuality Scale [41]; Closeness and interconnection – Inclusion of Other in Self Scale [42]; Empowerment /Self-efficacy – General Self-efficacy Scale [43]; Health status – EQ-5D-5L (EuroQol health measure with 5 levels of severity for 5 dimensions) [44]

Table 2 presents the measures used to assess the potential effectiveness of the DemPower app and provide information for the design of any future randomized controlled trial (RCT), including sample size estimation.

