### Data Collection

An evaluation questionnaire will explore participants’ experiences with the guide, relevance of guide’s contents, usability of the app, perceived benefits, relevance of the guide in everyday living, applicability to various contexts, the volume of contents, and the time required to complete the guide (Multimedia Appendix 1). Responses to questions may vary from rating, multiple choices to descriptive forms.

At the end of each section, written instructions will be provided, guiding participants to use a particular set of questionnaires. Questionnaires are split across 4 themes presented in the guide (Multimedia Appendices 2-5). Researchers will follow up on participants’ progress with the questionnaires during regular telephonic conversations or home visits and offer support if required.

The following usage data will be stored on the tablet to measure how the app is used:

The number of times and timestamp of when each screen was viewedThe number of times the initial splash or landing screen has opened, in order to tell how many times app was started from scratchThe contents pages will indicate how users are navigating the app, whether by the contents pages or going through sequentially using next or back buttons.

The outcome measures, questionnaires, and usage tracking data will form primary sources of data for this part of the study. All the questionnaires will be administered using an offline or a paper-based survey tool. The researcher will administer the outcome measures listed in Table 2 at baseline (prior to introducing the guide) and at the end point. Participants who choose to engage with only parts of the intervention will also be assessed at the start and at the time that they declare as completed or at the end of 3 months from the intervention initiation date. The details of participants’ progress, telephonic follow-ups, home visits, and variations in follow-up time frames will be recorded in the researchers’ logs. Researchers will support the person with dementia as he or she completes the outcome measures at baseline and at the end point during face-to-face meetings. Spouse or partner caregivers will be encouraged to complete the assessments on their own during the researcher’s visit.

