### Data Analysis

All the data obtained from outcome measures and evaluation questionnaires will be entered into an Excel or Stata database for further statistical analysis. The data will be anonymized prior to being uploaded to a database. The qualitative or open-ended responses from evaluation questionnaires will be categorized and analyzed thematically. The data from Sweden will be transferred to the research team at the University of Manchester for statistical analysis.

Given that this is a feasibility study (and that there is no control group), we will not be carrying out hypothesis testing to determine if the intervention is effective. Instead, we will focus on (1) estimating recruitment and attrition rates; (2) determining whether there is sufficient change in potential outcome measures following the intervention, using appropriate descriptive measures of central tendency (mean, median) and spread (standard deviation, inter-quartile range, range); (3) estimating the standard deviation of potential outcome measures to inform or refine a sample size calculation for the Phase III trial; and (4) estimating response rates to participant questionnaires, checking for floor and ceiling effects and in fact whether the intervention is acceptable to participating couples. We will reconsider the use of questionnaires or other items if the amount of missing data exceeds 10%.

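### Table 1 measures implementation by completion of every section, although couples may use a selection, and it pairs that outcome with dropout rates, mixing app use with study retention

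*Protocol article*

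**What the plan says.** Four places in the protocol article describe how much of the guide couples use and how that is judged.

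- **Abstract, Methods:** couples have 3 months with the app. The time taken to finish will be reviewed and may be shorter or longer than that.
- **DemPower Intervention:** a pace is suggested ("We will recommend the participants to engage with two sections per week"). Couples then get a free choice: "They have the option to engage with a selection of sections or with the entire guide and in any order". The next sentence reads "Participants are expected to complete the guide within a period of 3 months from the date of device activation".
- **Table 1, Implementation and practicality:** the outcome is "Willing and able to complete all the sections of the self-help guide", and its data source entry is "Dropout rates usage tracking data".
- **Data Collection:** those who use only parts of the guide have their end-point assessment "at the time that they declare as completed or at the end of 3 months from the intervention initiation date".

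Data Analysis lists "estimating recruitment and attrition rates" among its aims. Future Work says that recruitment and attrition will inform the power calculation of the full trial. Feasibility Design Process requires the study to be placed in one of four categories, from stopping to continuing unchanged.

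**The concern.** A couple that picks the sections relevant to it, uses them and attends the end-point visit has done what the intervention section allows. It still does not meet the Table 1 outcome. A couple that found the guide too hard and gave up does not meet it either. The outcome therefore puts permitted choice and failure to engage in the same group.

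The data source entry adds a second difficulty. Dropout normally means leaving the study or missing the end-point assessment, while usage tracking concerns contact with the app. A couple can stop using the app and remain in the study, so the two sources answer different questions.

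Uptake and completion are main results of a feasibility study. A low all-section figure could mean that the guide is not feasible in its present form, or only that couples chose what suited them. These readings point to different categories in the four-way decision. For the full trial's sample size, the figure needed is loss of outcome data, which should not be mixed with partial use of the app.

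**Working it through.** **Inputs from the document.** The recruitment target is 25 couples in the United Kingdom and 25 in Sweden, so 25 + 25 = 50, as stated under Sample Size. The article gives no completion rate, dropout rate or completion threshold. The number of sections is not in the text (Figure 2 is not shown), so the suggested pace cannot show whether the whole guide fits into 3 months.

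**Step 1: classify three kinds of couple under the stated text.**

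| Couple | Allowed by DemPower Intervention? | Meets the Table 1 outcome? | Lost to follow-up? |
|---|---|---|---|
| Uses every section, attends end point | Yes | Yes | No |
| Uses chosen sections only, attends end point | Yes | No | No |
| Gives up early, attends end point | Partial use is allowed | No | No |

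Rows 2 and 3 give the same result on the Table 1 outcome and on retention, although they mean different things for feasibility.

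**Step 2: how far can permitted choice move the figure?** Let E be the share of the 50 couples who use the guide as permitted, and s the share of those who choose a selection. Both are assumptions.

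All-section completion = E × (1 − s)

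| E | s = 0 | s = 10% | s = 20% | s = 30% | s = 50% |
|---|---|---|---|---|---|
| 70% | 70% | 63% | 56% | 49% | 35% |
| 80% | 80% | 72% | 64% | 56% | 40% |
| 90% | 90% | 81% | 72% | 63% | 45% |

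Worked case: E = 80% is 40 couples. With s = 20%, 8 choose a selection and 32 complete every section, so 32/50 = 64%.

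**Step 3: compare with sampling error.** The Wilson 95% interval for 40/50 is 67.0% to 88.8%. The shift in the worked case is 80 − 64 = 16 percentage points, against 80 − 67.0 = 13.0 points down to the lower limit. The reading falls below that limit once 0.80 × (1 − s) < 0.670, that is, s > 1 − 0.670/0.80 = 0.1625, or about 16%. With s = 10% the reading (72%) stays inside the interval.

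**The case against.** The strongest reply is that nothing is mismeasured. Screen-level timestamps give the share completing every section correctly. Table 1 lists outcomes of interest without a threshold, and no completion rate is tied to the four-way decision, so nothing says that partial users will be treated as failures. This stands as far as it goes: the count would be right. What remains is that the count is labelled as willingness and ability, and permitted partial use breaks that link.

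A reader might go further and infer that attrition is hidden, because a couple losing interest can declare itself finished. For example, if 10 of 50 couples stop early and none, half or all of them declare completion, recorded dropout would be 10/50 = 20%, 5/50 = 10% or 0/50 = 0%. The document does not support that inference. Those figures treat stopping the app as study dropout and count dropout only from missed assessments, and the article gives no such definition. A couple assessed at the end point has outcome data and is rightly counted as retained. Nor does the text say that couples are told they may declare themselves finished; it only describes when partial users are assessed.

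A reader might also infer that choice and abandonment can never be separated. That is too strong. Timestamps can show when use stopped. Researcher logs cover progress, calls and visits, and the questionnaires cover relevance and volume of content. These may show reasons, and the appendices are not available here, so it cannot be said that they omit them.

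Finally, operational definitions are often left to a full protocol, so their absence from an article is not a fault. The point does not rest on a missing definition. It rests on statements in the article that do not agree.

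**Conclusion.** The point holds as an inconsistency between the permitted use of the guide and the outcome by which implementation is judged. All-section completion is a sound description of use, but it is not a valid measure of willingness or ability while couples may choose sections. Pairing it with dropout mixes use of the intervention with retention in the study.

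The size is unknown because the share choosing a selection is unknown. With 80% of couples using the guide as permitted, selection shares of 10% to 50% give readings of 72% down to 40%. Above a selection share of about 16%, the shift exceeds the distance to the lower 95% limit around 40/50. All of these shares are assumptions; they show sensitivity and are not forecasts. No bias in the attrition figure is shown.

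**What to change.** Reconcile the statements in the Abstract (Methods), DemPower Intervention, Table 1 and Data Collection, so that permitted use, expected use, the 3-month period and the meaning of completion agree. Which level of use to expect is for the study team and is not proposed here.

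Replace the single Table 1 outcome with four quantities, each reported separately:

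1. the proportion of all sections opened or completed, per couple, from the usage log;
2. couples who finished the sections they chose;
3. couples who stopped using the app early, from the last-use timestamp read together with the sections still unused;
4. study withdrawal or missing end-point assessment, which is the attrition figure to carry to the full trial.

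At the monthly calls and the end-point visit, record a brief coded reason for skipping sections or stopping.

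The share of planned sections finished, with the plan updated each month, should not be the main measure. A couple losing interest could shorten its plan and still score 100%.

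The cost is protocol wording, one short item at contacts already scheduled and slightly longer calls. Self-reported reasons are imperfect and should be read alongside the log.
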